## **5.Product Features, Structural Composition, Working Principle, Mechanism of Action, and Testing Scope**

## 5.1 Product Features

The Annuloplasty Ring for cardiac valve repair features a nitinol tube as its base. The ring adopts a three-dimensional oval shape, conforming to the physiological structure of the tricuspid annulus. The ring is pre-mounted on a holder for ease of implantation. Clinically, it is used to correct and remodel pathological annuli, maintaining optimal leaflet coaptation.

## 5.2 Structural Composition, Working Principle, and Mechanism of Action

The Annuloplasty Ring comprises the following layers:

**Base layer:** A closed-loop nitinol tube connected with nitinol wires. **Intermediate layer:** A silicone layer with a suture border, filled with long-term implantable silicone between the base and intermediate layers. **Outer layer:** A biocompatible polyester fabric. The Annuloplasty Ring is designed for tricuspid valve repair. Its three-dimensional oval shape matches the natural tricuspid valve orifice. The ring comes pre-attached to a sterile, single-use holder for simplified implantation. The holder and sizing device are packaged separately as non-sterile components, requiring cleaning and steam sterilization before reuse.

prosthetic ring

[figure not shown]

**Figure 1: Schematic of Annuloplasty Ring Components**

[figure not shown]

**Figure 2: Annuloplasty Ring Schematic**

[figure not shown]

**Figure 3: Annuloplasty Ring Schematic**

[figure not shown]

**Figure 4: Holder Handle Schematic**

### 5.3 Testing Scope

Applicable to patients with tricuspid regurgitation who are eligible for Annuloplasty Ring implantation.

## 6. Indications, Contraindications, Precautions

### 6.1 Indications

The Annuloplasty Ring is indicated for: Correction of annular dilation. Enhancement of leaflet coaptation and annular stabilization. Prevention of further annular expansion.

### 6.2 Contraindications

**6.2.1** Pediatric patients with potential somatic growth affecting valve area.

**6.2.2** Active bacterial endocarditis during device implantation.

### 6.3 Precautions

**6.3.1** Surgeons must receive procedural training prior to clinical use.

**6.3.2** The sizing device and holder handle must be cleaned and steam-sterilized for reuse.

**6.3.3** Ring sizing must follow precise annular measurements using the manufacturer-provided sizing device. Do not use the holder as a sizing tool.

**6.3.4** Avoid using sharp needles or metal forceps on the ring during implantation to prevent damage.

**6.3.5** Sutures must not penetrate atrial tissue or coronary arteries (left circumflex or right coronary artery) to avoid conduction system injury.

**6.3.6** Remove the holder before closing the surgical site. If retained, the holder may cause severe injury or death. Use intraoperative X-ray to confirm removal if necessary.

**6.3.7** Postoperative anticoagulation therapy is recommended. Prophylactic antibiotics are advised for patients undergoing dental or invasive procedures with bacteremia risk.

## **6.4 Storage and Transportation**

**Storage:** Store at room temperature in a dry, uncontaminated environment. Do not use expired products.

**Transportation:** Avoid impact, compression, or exposure to moisture. Discard the product if damaged during transit.

## **6.5 Complications**

**6.5.1** Severe complications, including death, may arise from adverse reactions to the implant, necessitating reoperation or device replacement.

**6.5.2** Surgical complications include, but are not limited to:

**Residual or recurrent valve regurgitation:** The valve may continue to leak or start leaking again after surgery.

**Valve stenosis:** The valve may become narrowed, restricting blood flow.

**Thrombosis:** Blood clots may form, potentially blocking blood flow.

**Hemolysis:** Red blood cells may break down abnormally.

**Atrioventricular (AV) block:** The electrical signals in the heart may be disrupted, affecting heart rhythm.

**Low cardiac output:** The heart may not pump enough blood to meet the body's needs.

**Right heart failure:** The right side of the heart may fail to function properly.

**Degenerative changes or dysfunction of the natural valve:** The patient's own valve may deteriorate or malfunction due to worsening disease.

**Endocarditis:** An infection of the heart's inner lining or valves.

Incomplete repair of the valve or subvalvular structures: The repair may not fully correct the valve or its supporting structures.

Coronary artery injury caused by sutures: The stitches used during surgery may damage the coronary arteries.

Complications from prolonged cardiopulmonary bypass or aortic cross-clamping: Extended use of the heart-lung machine or restricted blood flow during surgery may cause complications.

Inadequate myocardial protection: The heart muscle may not be sufficiently protected during surgery, leading to damage.

Tearing of the polyester fabric due to sharp needles: The fabric used in the device may tear if sharp needles are used improperly.

Suture breakage due to improper placement in the Annuloplasty Ring: Stitches may break if they are not placed correctly in the ring.

Bleeding caused by anticoagulation therapy: Blood-thinning medications may lead to excessive bleeding.

Local or systemic infections: Infections may occur at the surgical site or spread throughout the body.

**6.5.3** Device-related complications include, but are not limited to:

Residual or recurrent valve regurgitation: The valve may continue to leak or start leaking again after surgery.

Valve stenosis: The valve may become narrowed, restricting blood flow.

Thrombosis: Blood clots may form, potentially blocking blood flow.

Hemolysis: Red blood cells may break down abnormally.

Atrioventricular (AV) block: The electrical signals in the heart may be disrupted, affecting heart rhythm.

Low cardiac output: The heart may not pump enough blood to meet the body's needs.

Right heart failure: The right side of the heart may fail to function properly.

Degenerative changes or dysfunction of the natural valve: The patient's own valve may deteriorate or malfunction due to worsening disease.

Endocarditis: An infection of the heart's inner lining or valves.

Incomplete repair of the valve or subvalvular structures: The repair may not fully correct the valve or its supporting structures.

Coronary artery injury caused by sutures: The stitches used during surgery may damage the coronary arteries.

Complications from prolonged cardiopulmonary bypass or aortic cross-clamping: Extended use of the heart-lung machine or restricted blood flow during surgery may cause complications.

Inadequate myocardial protection: The heart muscle may not be sufficiently protected during surgery, leading to damage.

Tearing of the polyester fabric due to sharp needles: The fabric used in the device may tear if sharp needles are used improperly.

Suture breakage due to improper placement in the Annuloplasty Ring: Stitches may break if they are not placed correctly in the ring.

Bleeding caused by anticoagulation therapy: Blood-thinning medications may lead to excessive bleeding.

Local or systemic infections: Infections may occur at the surgical site or spread throughout the body.

**6.5.4** Report all complications to PerMed immediately: [contact]; [contact].

## **7. Overall Trial Design**

### **7.1 Trial Design**

#### **7.1.1 Objective**

To evaluate the safety and efficacy of the Annuloplasty Ring, developed by PerMed Bio-Medical Engineering Co., Ltd., Beijing, for treating tricuspid regurgitation.

**7.1.2** This trial is designed as a prospective, multicenter, randomized controlled clinical trial to evaluate the safety and efficacy of the Annuloplasty Ring for tricuspid regurgitation.

Rationale:

##### **7.1.2.1 Prospective, Multi-Center Design**

**Prospective:** This means the trial plan is designed and finalized before the study begins. This approach is standard for pre-market clinical trials of medical devices, as it ensures a clear and structured process for evaluating safety and effectiveness.

**Multi-Center:** The trial will be conducted across more than ten clinical sites nationwide. By involving multiple centers, the study can include a more diverse and representative group of participants. This reduces the risk of bias that might occur if

the trial were conducted at a single center, making the results more reliable and credible.

#### **7.1.2.2 Rationale for Randomized Controlled Design**

The randomized controlled trial (RCT) design is chosen because it provides a high level of reliable evidence in clinical research. In this trial, participants who meet the inclusion criteria will be randomly assigned to one of two groups:

Test Group: Participants will receive the trial Annuloplasty Ring.

Control Group: Participants will receive a commercially available Annuloplasty Ring (manufactured by Edwards, which has been approved by the National Medical Products Administration (NMPA). This control device is widely used in clinical practice and has a well-established efficacy profile. Random assignment ensures balanced and comparable groups, minimizing bias and enhancing the reliability of the results.

Dynamic Randomization: The trial uses a dynamic randomization method, taking into account two key factors:

Study Center: Ensures balanced distribution across multiple sites.

Severity of Regurgitation: Participants are stratified based on the degree of valve leakage (mild, moderate, or severe).

Central Randomization System: The trial employs a Clinical Trial Central Randomization System (DAS for IWRS) to allocate random numbers, ensuring fairness and transparency in group assignment.

#### **7.1.2.3 Rationale for Selecting the Primary Endpoint:**

The primary goal of the Annuloplasty Ring is to repair and reshape the diseased valve annulus, ensuring proper leaflet coaptation (the area where the valve leaflets meet). For patients with tricuspid regurgitation (leaky valve), the main evaluation metric after annulus repair is the success rate of the Annuloplasty Ring at 6 months post-surgery. Definition of Repair Success: No Severe Regurgitation: Postoperative echocardiography (heart ultrasound) must show no severe valve leakage. Annular Dilation  $\leq 15\%$ : The increase in the annular size (measured by echocardiography) must be 15% or less compared to preoperative measurements.

Secondary Efficacy Endpoints

The secondary endpoints for evaluating effectiveness include the following assessments at discharge or 30 days post-surgery (whichever comes first), and at 3 months, 6 months, and 12 months post-surgery:

Degree of Valve Regurgitation: Assessed by echocardiography (heart ultrasound) to measure the severity of valve leakage.

Echocardiographic Parameters: Changes in the following measurements will be evaluated:

Size of the right atrium and right ventricle.

Annular dimensions (diameter).

Width of the narrowest part of the regurgitant jet.

Area of reverse blood flow.

NYHA Functional Class: A measure of heart failure symptoms and functional capacity, classified as Class I (no symptoms) to Class IV (severe symptoms).

Freedom from Reoperation: The rate of patients who do not require repeat surgery for tricuspid regurgitation.

Device Performance Evaluation:

Suture Needle Ease of Use: How smoothly the needle passes through the Annuloplasty Ring during implantation.

Holder Device Usability: How user-friendly the ring holder is during the procedure.

Surgical Technical Success:

Defined as the following criteria being met before leaving the operating room:

No intraoperative death.

Successful implantation of the Annuloplasty Ring.

Successful removal of the ring holder.

No need for emergency surgery or additional interventions related to the investigational device.

Safety Endpoints:

Safety will be assessed at discharge or 30 days post-surgery (whichever comes first), and at 3 months, 6 months, and 12 months post-surgery. The following will be evaluated:

Serious Adverse Events (SAEs): Including:

Cardiovascular-related deaths linked to the device.

Major bleeding linked to the device.

Severe damage to the heart or other body structures linked to the device.

Infective endocarditis (heart infection) linked to the device.

Thromboembolic events (blood clots) linked to the device.

All-Cause Mortality: Death from any cause during the study period.

Device-Related Adverse Events: Any complications or issues directly related to the device.

Device Defects: Any malfunctions or failures of the device.

Follow-up content includes clinical symptoms and signs, laboratory examinations, ECG, CDFI, recording adverse events, etc., to verify the safety and effectiveness of the trial cardiac Annuloplasty Ring.

### **7.1.3 Measures to Reduce and Avoid Bias**

To ensure the reliability and validity of the trial results, bias will be minimized through the following three key strategies:

#### **Randomization Design**

The trial is designed as a randomized controlled trial (RCT), which is the gold standard for minimizing bias in clinical research. After a participant (or their legal guardian) signs the informed consent form and meets the eligibility criteria, they will be randomly assigned to either the test group or the control group using a centralized randomization system. This approach ensures that the two groups are balanced and comparable, reducing the risk of bias and improving the reliability of the results.

#### **Investigator Training**

Before the trial begins, the sponsor and clinical monitors will work with the principal investigators at each trial site to provide comprehensive training on the trial protocol.

Investigators will be trained to: Understand and properly use the investigational product. Stay informed about any new information or updates related to the product during the trial. This ensures that all investigators follow the same procedures and maintain consistency across all trial sites.

#### **Clinical Trial Monitoring**

A monitoring plan will be established, and qualified monitors appointed by the sponsor will conduct regular on-site visits to the trial hospitals. The monitors will:

Ensure that the trial protocol is strictly followed at all sites. Verify that the data recorded in the electronic Case Report Forms (eCRFs) match the original source documents (e.g., medical records). This oversight helps maintain the integrity of the trial data and ensures compliance with regulatory and ethical standards.

#### **7.1.4 Investigational and Control Devices**

During surgery, the measurement of the tricuspid complex septal base length serves as a criterion for selecting the appropriate annulus size. Based on the results of randomization, the tricuspid Annuloplasty Ring from the appropriate test or control group is then selected.

Investigational Device: Annuloplasty Ring (Beijing Permed Biomedical Engineering Co., Ltd.) / (sizes 26、28、30、32、34、36).

Control Device: Edwards MC3 Ring (Edwards Lifesciences (Shanghai) Medical Products Co., Ltd.) / (sizes T26–36).

The control device is the device that has been approved for marketing by the National Medical Products Administration, and the usage method can be found in the product instruction manual.

Instructions for use of Annuloplasty Ring used in the trial:

##### **7.1.4.1 Annular Measurement and Selection of the Annuloplasty Ring**

Measuring the Tricuspid Valve Size:

The size of the tricuspid valve annulus is measured using a sizing device. The selection of the Annuloplasty Ring is primarily based on the dimensions of the septal leaflet attachment site. The sizing device has two notches on its straight segment, which are used to measure the annular dimensions. If the septal leaflet's contour is not clearly visible, the sizing device can also be used to measure the anterior leaflet and its surface area. These measurements help determine the appropriate size of the Annuloplasty Ring. To ensure accurate measurements, a nerve hook can be used to gently pull on the chordae tendineae attached to the anterior papillary muscle. This maneuver helps stretch and flatten the valve leaflets, making it easier to measure the annulus accurately.

##### **7.1.4.2 Using the Ring Holder and Holder Handle**

Recommendation for Use: During the implantation of the Annuloplasty Ring, it is recommended to use the ring holder and holder handle to assist with the procedure. The holder handle is packaged separately in a non-sterile condition and must be

cleaned and sterilized before use. To use the holder handle, connect the handle's latch to the ring holder. The holder handle features a bendable nitinol rod, which allows the handle to be adjusted to different angles to meet the needs of various surgical approaches. The nitinol rod has a shape memory property, meaning it will return to its original shape after being bent and sterilized using high-temperature steam. This feature allows the handle to be reused multiple times.

#### Separating the Ring Holder and Handle:

To detach the ring holder from the handle:

Hold the ring holder with one hand.

Pull the holder handle backward with the other hand.

The ring holder is for single use only and must be disposed of as medical waste after the procedure.

The holder handle can be cleaned, sterilized, and reused.

#### Inspection and Maintenance:

Regularly inspect the holder handle for any signs of damage, such as dullness, cracks, or wear. If any damage is found, immediately replace the handle. For replacement, contact the local representative of PerMed.

### **7.1.4.3 Implantation of the Annuloplasty Ring**

The Annuloplasty Ring is implanted by placing interrupted horizontal mattress sutures through the fibrous annulus. Avoid passing sutures through the His bundle area to prevent damage to the heart's electrical conduction system. To ensure proper exposure of the ring and avoid interference with the chordae tendineae, follow these steps: Gently pull the valve leaflets in a direction perpendicular to the atrial wall. Pass the suture needle from the ventricular side through the annulus, then return it toward the atrial side. Regardless of the specific technique used, the following principles must always be followed:

**7.1.4.3.1** Ensure that each valve leaflet is accurately aligned with the corresponding segment of the Annuloplasty Ring.

**7.1.4.3.2** Sutures should pass through the ring 2 mm away from the leaflet attachment site to preserve the natural function of the leaflets.

**7.1.4.3.3** The first suture should be placed at the center of the septal leaflet to ensure proper positioning and stability of the ring.

### **7.1.4.4 Suturing the Annuloplasty Ring**

The Annuloplasty Ring features a suture border designed to facilitate easy passage of sutures. As shown in Figure 5, if resistance is encountered while passing the needle through the ring, withdraw the needle and reinsert it through the suture border. A green circular marking on the ring indicates the location of the suture border, aiding in proper suture placement. Sutures should be placed between the two commissures and aligned with the corresponding segments of the Annuloplasty Ring. The remaining part of the annulus should be positioned to match the size and shape of the ring, ensuring a proper fit.

#### **7.1.4.5 Removing the Ring Holder**

The ring holder features a central fixation wire at its core. To remove the holder, simply cut this fixation wire. When the holder is removed, all fixation wires are also taken out with it. After removal, the ring holder must be discarded as medical waste. Do not cut any other fixation wires besides the central one, as cutting additional wires could cause them to detach and enter the heart chamber, potentially leading to thrombus formation.

#### **7.1.4.6 Evaluating the Repair Outcome**

During tricuspid valve repair, intraoperative echocardiography is utilized to assess the function of the valve and the quality of the repair. To achieve optimal results, the following steps are critical: accurate measurement of the valve orifice size, proper selection of the Annuloplasty Ring, and optimal implantation technique. If damage to the structures below the valve is detected, additional surgical interventions may be required. After carefully measuring the size, the Annuloplasty Ring is implanted, if direct visual inspection and/or intraoperative testing still indicate that the valve regurgitation is not fully corrected, the surgeon must be prepared to remove the Annuloplasty Ring and perform artificial heart valve replacement during the same surgery.

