| 
Statistical Methods:
 
This trial plans to enroll 164 patients, who will be randomly assigned to either the experimental group or the control group in a 1:1 ratio, with 82 cases in each group.
 
The primary endpoint of this clinical trial is the success rate of valve repair at 6 months postoperatively, defined as no severe regurgitation and an increase in annular diameter of <math>\leq 15\%</math> based on echocardiographic evaluation. According to literature reports and clinical experience, the expected success rate of valve repair in the control group at 6 months postoperatively is 95%. Assuming that the investigational medical device can achieve comparable efficacy, the clinically accepted non-inferiority margin is set at -10%. With a one-sided significance level of 0.025 and a power of 80%, the sample size was estimated using PASS 14.0 software, indicating that 75 cases are required for each group. Considering potential dropouts during the study, the plan is to enroll 82 cases per group, totaling 164 cases.
 
The trial results will be determined based on the difference in the primary efficacy endpoint between the experimental group and the control group. If the lower limit of the 95% confidence interval for the difference in success rates between the experimental group and the control group is
 |                                                                                                                                                                                                                                                                                                                                                                                                                                                                                                                                                                                                                                                                                                                                                                                                                                                              |

greater than -10% (the predefined non-inferiority margin), the non-inferiority conclusion will be established. Otherwise, the non-inferiority conclusion will not be supported.

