### 7.1.6.2 Methods and Timing for Evaluating, Recording, and Analyzing Efficacy Parameters

**7.1.6.2.1** Valve annuloplasty repair success is defined as no severe regurgitation and an increase in diameter  $\leq 15\%$  (based on a comprehensive assessment of regurgitation severity and diameter increase).

Tricuspid Regurgitation Assessment Index Table

| Parameter                   | None                                     | Trace                                                        | Mild               | Moderate                                            | Severe                 |
|-----------------------------|------------------------------------------|--------------------------------------------------------------|--------------------|-----------------------------------------------------|------------------------|
| Regurgitation Jet           | No regurgitation jet in the right atrium | Regurgitation jet extends $\leq 1$ cm from the valve orifice |                    |                                                     |                        |
| Absolute Regurgitation Area |                                          |                                                              | $< 5 \text{ cm}^2$ | $5 \text{ cm}^2 \leq \text{area} < 10 \text{ cm}^2$ | $\geq 10 \text{ cm}^2$ |
| Regurgitation Area Fraction |                                          |                                                              | $< 20\%$           | $20\% \sim 33\%$                                    | $\geq 33\%$            |

Absolute regurgitation area: Measured by TTE or TEE in the standard view with the most regurgitation.

Regurgitation area fraction: Measured by TTE in the apical four-chamber view or TEE in the mid-esophageal four-chamber view, or in the standard view with the most regurgitation.

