### **7.2.2 Surgical Treatment (Day 0, Surgery Day)**

**7.2.2.1** Monitor vital signs (blood pressure, pulse).

**7.2.2.2** Perform surgery using the designated device according to randomization results, recording anesthesia method, device model, and device performance evaluation.

**7.2.2.3** Transesophageal echocardiography (TEE) or transthoracic echocardiography (TTE) evaluation as needed.

**7.2.2.4** Record intraoperative complications and adverse events.

**7.2.2.5** Record intraoperative antiplatelet or anticoagulant medications.

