## **8.2 Calculation of sample size**

### **8.2.1 Total sample size**

According to literature reports and clinical experience, it is estimated that the success rate of valve repair with a prosthetic ring in the control group 6 months post-surgery is 95%, with a non-inferiority margin of -10%. Using a one-sided test,  $\alpha=0.025$ ,  $\beta=0.2$  (power 80%), the trial group and control group are to be matched at a ratio of 1:1. Using PASS 14.0 software, it is estimated that each group will require 75 cases. Considering the risk of dislodgement during the study process, it is planned to enroll 82 cases in each group, totaling 164 cases.

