### **8.9 Selection criteria and reasons for subjects included in the analysis**

Full analysis set (full analysis set, FAS): The collection of all cases randomized to the group and who received surgical implantation devices.

Conformity set (per protocol set, PPS): A subset of the full analysis set, a data set generated by subjects who are fully compliant with the protocol, compliance including treatment received, availability of measurement of primary endpoint indicators, and no significant deviation from the protocol. PPS analysis is used for primary efficacy endpoints.

Safety Dataset (safety set, SS): All actual data that were randomly enrolled and underwent surgical implantation of devices and had post-implant safety metrics recorded. SS analysis was used for primary safety metrics.

Efficacy analysis will be performed on the full analysis set and the compliant set. All baseline demographic data analysis will be performed on the full analysis set and safety evaluation will be performed on the safety set.

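### The primary endpoint does not say how to score a patient whose ring is removed and whose valve is replaced during the index operation, and read literally it can count that patient as a repair success

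*Protocol*

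**What the plan says.** Section 7.1.4.6 describes the case where a ring has been implanted and direct inspection or intraoperative testing still shows regurgitation: "the surgeon must be prepared to remove the Annuloplasty Ring and perform artificial heart valve replacement during the same surgery".

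Section 7.1.6.2.1 sets the primary outcome: "Valve annuloplasty repair success is defined as no severe regurgitation and an increase in diameter" of at most 15%. Sections 7.1.6.1 and 7.1.8 and the synopsis repeat the same two criteria. Section 7.1.6.2.2 measures the diameter increase from the 3-month echo to the 180-day echo, whereas section 7.1.2.3 measures it from the preoperative value.

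Section 8.9 defines the full analysis set (FAS) as "The collection of all cases randomized to the group and who received surgical implantation devices". The per-protocol set (PPS) is a subset that requires compliance, including with the treatment received. Section 8.7 fills missing primary data by last observation carried forward.

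On the devices, section 7.1.4 places 7.1.4.1 to 7.1.4.6 under the instructions for the ring under trial. For the control ring it says that "the usage method can be found in the product instruction manual". The procedures for the day of surgery, which apply to both arms, read "Transesophageal echocardiography (TEE) or transthoracic echocardiography (TTE) evaluation as needed" (7.2.2.3). Note 2 to the flowchart in 7.2.8 recommends intraoperative TEE.

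**The concern.** Removing the ring for a prosthetic valve is the clearest way in which a ring can fail to repair the valve, and the protocol itself foresees it. The trial asks whether the test ring repairs as well as the control ring. If the prosthesis's good 6-month echo is credited to the ring that was taken out, or the patient is left out, the comparison is biased toward non-inferiority whenever the test ring is converted more often. Non-inferiority on this endpoint is the criterion for a qualified result (8.5), and with about four expected failures per arm, a few patients can decide it. The surgeon knows which ring is being used, so how these patients are scored should be fixed before any results are seen.

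**Working it through.** **Where a conversion would show.** Take a patient whose ring is replaced by a prosthesis in the index operation and whose prosthesis works at 6 months.

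| Place in the protocol | Effect on this patient |
|---|---|
| 7.1.6.2.1, 7.1.8 (primary endpoint) | Two echo criteria; nothing requires the ring to be present |
| 7.1.6.2.2 (3-month baseline) | Both echoes fall after the conversion, so a stable prosthesis would normally pass |
| 7.1.2.3 (preoperative baseline) | Conflicts with 7.1.6.2.2, but does not exclude a pass either |
| 8.7 (carry-forward) | Not triggered, because the 6-month echo is observed |
| 8.9 (FAS) | Silent on a ring implanted and then removed; inclusion is the natural reading |
| 8.9 (PPS) | May drop the patient for the treatment received |
| Freedom from reoperation | Not registered, because it is the same operation |
| Technical success (7.1.6.2.6) | Naturally a failure, although removal of the ring is not named |

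**The plan's own sample size.** Inputs from 8.2.1: 95% success in control (test assumed equal), margin 10 points, one-sided alpha 0.025, power 80%.

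n = (1.960 + 0.842)² × 2 × 0.95 × 0.05 / 0.10² = 74.6, so 75 per group, as stated. The planned 82 per group allows for 1 - 75/82 = 8.5% loss, near the 10% in 8.4. The sample size is not in dispute.

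**Effect on the decision.** Section 8.1.5 specifies the Newcombe 95% interval. Its lower limit is

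L = (p1 - p2) - √[(p1 - l1)² + (u2 - p2)²],

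where l1 is the Wilson lower limit for the test arm and u2 the Wilson upper limit for control. At the planned rate, 0.95 × 82 = 77.9, so 78/82 is used.

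| Successes of 82 | Rate | Wilson 95% limits |
|---|---|---|
| 78 | 95.12% | 88.12% to 98.09% |
| 77 | 93.90% | 86.51% to 97.37% |
| 76 | 92.68% | 84.94% to 96.60% |
| 75 | 91.46% | 83.41% to 95.80% |

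- 78 v 78: 0 - √(7.00² + 2.96²) = -7.6%
- 76 v 78: -2.44 - √(7.74² + 2.96²) = -10.7%

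Now suppose that 78/82 in each arm includes conversions scored as successes, and rescore them as failures:

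| Conversions, test / control | Successes, test v control | Lower limit | Against -10% |
|---|---|---|---|
| 0 / 0 | 78 v 78 | -7.6% | pass |
| 1 / 0 | 77 v 78 | -9.2% | pass |
| 2 / 0 | 76 v 78 | -10.7% | fail |
| 3 / 0 | 75 v 78 | -12.2% | fail |
| 2 / 1 | 76 v 77 | -9.7% | pass |
| 2 / 2 | 76 v 76 | -8.7% | pass |

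The totals matter as well as the difference: 3 / 2 gives -1.22 - √(8.05² + 3.92²) = -10.2%. If test-arm conversions are left out of the denominator instead, one, two or three give -7.7%, -7.9% and -8.0%, all passing.

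**Effect on the error rate.** Exact binomial enumeration was used with 82 per arm and true success of 85% v 95% when conversions count as failures, which is the margin itself. The chance of wrongly concluding non-inferiority is then 2.4%. If part of the 10-point deficit is conversions handled otherwise:

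| Points of deficit that are conversions | Scored as success | Left out |
|---|---|---|
| 1 | 3.8% | 3.7% |
| 2 | 5.9% | 5.1% |
| 3 | 9.0% | 7.6% |
| 5 | 19.5% | 16.1% |

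**The case against.** The protocol is not blind to conversion. Technical success is an efficacy endpoint compared between arms (8.1.6.1.4), and on its natural reading a ring taken out for a prosthesis fails it. A converted patient with severe regurgitation at 6 months also fails the primary endpoint. A reader might infer that a conversion can never count as a failure; the text does not support that.

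The endpoint is also named a success rate of annuloplasty repair, and in section 8 of repair with a prosthetic ring, so an assessor could properly score a replaced valve as a failed repair. That stands as a possible reading, but no criterion says so and the literal criteria point the other way.

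Section 8.1.2 leaves the detailed classification of analysis sets to the SAP, which is not at hand. That is a fair answer on FAS and PPS membership alone. It does not cover what counts as repair success, which the protocol itself defines.

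A reader might also infer that the conversion rule differs by arm. This is not shown. The control ring's manual is not part of the protocol and may carry the same instruction, and 7.1.4.6 asks the surgeon to be prepared rather than stating when to convert.

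Finally, the numerical scenario loads conversions onto the test arm, and two extra test-arm failures from any cause would move the limit equally. Both are true. The difference is that these two patients' classification is left open.

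**Conclusion.** The gap is real and confined to the primary endpoint and its analysis sets. The protocol foresees conversion in the index operation but does not classify it. Applied literally, with the 3-month diameter baseline, the definition can credit a working prosthesis to the removed ring.

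The size depends on assumptions, because the protocol gives no conversion rate. At 78/82 in each arm, two test-arm conversions with none in control decide the result; one does not, nor do two in each arm. The bias favours non-inferiority only if the test ring is converted more often, which nothing in the protocol establishes.

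On the arms, the supported conclusion is narrower: the protocol does not make clear which intraoperative assessment and conversion instructions apply to both.

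**What to change.** Add to 7.1.6.2.1, 7.1.8 and 8.9: a patient who leaves the operating room without a ring of the randomised type in place is a primary-endpoint failure in the arm as randomised and stays in the FAS; a different size of the assigned ring is not a failure. Report conversions by arm.

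Separately, reconcile 7.1.4, 7.1.4.6, 7.2.2.3 and Note 2 of 7.2.8, so that it is clear what intraoperative assessment and conversion instructions apply to both arms. The clinical rule is for the sponsor and surgeons to decide; none is proposed here.

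The cost is a few sentences. No new data are needed, since 7.2.2 already records the device model and intraoperative complications and adverse events. The downside is a possibly slightly lower success rate in either arm.
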